## Abstract

**Background:**

Complex brain arteriovenous malformations (bAVMs) in ≥3 Spetzler-Martin grades have long been challenges among cerebrovascular diseases. None of the traditional methods, such as microsurgical operation, endovascular intervention, or stereotactic radiotherapy, can completely eliminate complex bAVMs without a risk of neural function deterioration. The multistaged hybrid operation solved part of the challenge but remained risky in the installment procedures and intervals. The one-staged hybrid operation was applied in the surgical treatment of cerebrovascular diseases and proved to be a potentially safe and effective method for curing complex bAVMs. However, lacking the support of high-level evidence, its advantages remain unclear. This study was proposed to validate the benefits and risks of one-staged hybrid operation in the treatment of complex bAVMs, as well as its indications, key technologies, and workflows.

**Methods:**

The study is being conducted from Jan 2016 to Dec 2020 with 20 cooperation centers. It consists of 2 sets. The registry set is designed as a prospective real-world registry. The trial set is designed as a prospective pragmatic clinical trial, specifically for the patients with perforating arterial feeders. The two sets share a common grouping: the traditional operation group and the one-staged hybrid operation group. The assignment is based on the clinical condition in the registry set and is randomized in the trial set. End points will be evaluated at scheduled time points. The safety and efficiency of one-staged hybrid operation in treating complex bAVMs will be validated.

**Discussion:**

The study is designed for a real-world exploration of benefits and risks of one-staged hybrid operation in the treatment of complex bAVMs. The two-set design reduces the compromise of clinical practice due to the study and improves the statistical power and research quality with a practical sample size. In the study, advantages of the one-staged hybrid operation will be evaluated and compared to those of traditional operation. A spanning development of neurosurgical operation might be facilitated by the study, which means a higher cure rate and lower disability rate in patients with complex bAVMs.

**Trial registration:**

The study was retrospectively registered in ClinicalTrials.gov (NCT03774017) on 11th Dec, 2018.

## Background

The surgical treatment of brain arteriovenous malformations (bAVMs) in deep and eloquent locations with complex angioarchitectures has long been a challenge [1–4]. These bAVMs were usually ≥3 in Spetzler-Martin’s grading system. The neurosurgical operation used to be the most effective method of eliminating the bAVMs. With the consideration of neural function protection, it no longer worked, not even with the revolutionary microsurgical techniques [5–11], especially in the complex lesions [12]. On the other hand, endovascular embolization could eliminate the bAVMs directly by obliterating the feeding arteries and nidus without the destruction of local parenchyma [13]. With this feature, the neural function of the brain stem and other eloquence areas were partially preserved [14]. Despite the development of endovascular instruments, materials, and techniques [15–22], limitations of manipulation and prognosis essentially existed in complex bAVMs. Among a variety of suboptimal events, intraoperative bleeding and residue were the most remarkable ones [23, 24]. The cooperation of microsurgery and endovascular intervention typically showed up as several stages of endovascular embolization followed by a scheduled microsurgical resection or radiotherapy (AKA multistaged hybrid operation). It significantly reduced the rates of mortality, neural deficit and postoperative epilepsy in complex bAVMs [25–27]. However, the latent risks of multistaged hybrid operation should be alerted, such as the trap of catheters, intraoperative bleeding, and venous sinus thrombosis in installment treatments, as well as rebleeding, infarction, and epilepsy in intervals [28, 29]. These limitations were not overcome until the one-staged hybrid operation was introduced from cardiac operations [30]. The procedures of microsurgery and endovascular intervention were integrated together in one operation without the transfer of patients. These procedures were applied in the surgical treatment of cerebrovascular diseases and proved to be a potentially safe and effective method of curing complex bAVMs [31, 32].

As an innovative operation mode, no clinical research has been set up to investigate the benefits and risks of the one-staged hybrid operation in the treatment of complex bAVMs as compared to traditional methods. Only a few descriptive studies have been published since it appeared [31–33], and these can hardly be regarded as providing high-level evidence. In addition, indications, key technologies, workflows, etc. remained unclear. We proposed this study to solve the problems above.

The aim of this study is to validate the benefits and risks of the one-staged operating technique in the treatment of complex bAVMs. Operative indications, key technologies, and workflows will be further explored in our study.

## Methods

### Aims

To validate the benefits and risks of one-staged operating technique in the treatment of complex bAVMs, as well as the operative indications, key technologies, and workflows.

### Study design

The study consists of 2 parts: the registry set and the trial set. The two sets of this study share a common data pool, which contains all the enrolled patients. The registry set is designed as a multicentric, prospective, real-world registry (Research on Hybrid Operation Technique in the Treatment of Complex Brain Arteriovenous Malformations; ClinicalTrials.gov ID: NCT 03774017), and it occupies the whole data pool. The patients involved will receive traditional operation (TO) or one-staged hybrid operation (HO) and will be registered in the corresponding TO group or HO group. End points will be evaluated at scheduled time points. The safety and efficiency of the one-staged hybrid operation in treating complex bAVMs will be validated. The trial set is designed as a multicenter, prospective, pragmatic clinical trial (PCT). Patients in this set will be registered in the registry set in the meantime. PCT is a real-world modification of randomized clinical trial (RCT), consisting of an RCT part and a registry part. Patients have the right to choose the part in which they want to participate. The candidates in this set are patients harboring bAVMs with perforating arterial (PA) feeders. To them, an extra written informed consent is required. Patients who agree to take part in the RCT part will be randomly assigned to the HO or TO group and receive the corresponding treatment. Both of the sets share the same end points. The purpose of the trial set is to validate the benefits and risks of hybrid operation for lesions with perforating arterial feeders and the contribution of endovascular embolization. A strategy of multicenter stratified blocked randomization is used in the central randomization system (CRS), which is contained in Electrical Data Capture (EDC) system. When registering a participant in EDC system in the trial set, CRS generates an assignment result according to the demographic information. Each center is set as a stratifying level, which could reduce the differentiation of sample size between groups. The blind codes, generated by statistician, remain blind during randomizations to avoid potential selection bias. The design of this study is presented in Fig. 1. The grouping assignment is blinded to outcomes assessors. Both sets will be conducted between Jan 2016 and Dec 2020. The study is hosted by Beijing Tiantan Hospital, with the participation of 20 cooperation centers, including academic, military, and other public hospital (Table 1).

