### Group assignment and treatment

In the registry set, patients will be assigned to the TO group or the HO group on the basis of clinical conditions and personal wishes. Patients in the HO group will receive microsurgical operation under the assistance of endovascular embolization or balloon occlusion. Patients in the TO group will receive only traditional microsurgical operations, and a repeated DSA will be arranged 3 days after the operation.

In the trial set, patients who refuse the randomized group assignment will be enrolled in the registry set. Those who agree will be randomly (by central randomization system) assigned to the TO group or the HO group. The interventions of each group will be the same in the two sets.

The functional MRI-based neuro-navigation and intraoperative Doppler ultrasound will be used as essential assistance in all operations.

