### Sample size

#### Registry set

According to the relevant literature and data, the average morbidity rate of neural function deterioration is 38.6% [9–11, 34, 35]. The aim of the hybrid operation is to reduce the rate of neural function deterioration by 10%, referring to present studies [31–33]. To ensure the statistical power and the potency of exploring technical details, the sample size is set as the maximum operative capacity of participating centers. According to the records of the latest 5 years, the operative capacity of Beijing Tiantan Hospital is about 220 cases of bAVMs per year, and of other participating centers is 20 cases per year in total. A total of 1200 cases will be recruited into the cohort in the 5-year-recruitment. Among them, 800 cases will receive hybrid operations, and 400 cases will receive microsurgical operations.

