#### Trial set

Few studies have been found on bAVMs with perforating feeding arteries. Referring to relevant studies of bAVMs, the neural function deterioration rate was 38.6% in traditional operation and 19% in one-staged hybrid operation. By using PASS 14 (PASS Power Analysis and Sample Size software, NCSS, LLC, Utah, US) with a significance level of 0.05 and a statistical power of 0.9, the minimum sample size for each group is *n* = 117. In total, 236 patients will be enrolled in the trial set.

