### Statistical analyses

Statistical analyses will be conducted using the Statistical Package for the Social Sciences software (V.22.0; SPSS, Chicago, Illinois, USA). Demographic information (age, gender, race, provenance, occupation), medical histories (primary symptom, operation history, and past history, family history, smoking and drinking history), bAVM-related morphological and location features (eloquences and fiber tracks involved according to the task), angioarchitectural features (origin and type of feeding arteries, situation of nidus and draining veins), and admitting conditions (signs, mRS score and NIHSS score) will be cataloged into continuous or categorical variables and descriptively analyzed. The baseline conditions of cases involved in the two groups will be compared by the characteristics described above. The Chi-square test and Student t-test will be conducted between homogeneous cases of 2 groups in the outcome variables, including operation-related events (e.g., operative time, hemorrhagic volume, electrophysiological changes) and outcomes to make comparisons of their safety and efficiency in several aspects. Univariate and multivariate logistic regression analyses will be conducted to explore the correlations between the outcome index and variables above. Analyses of subgroups in the hybrid operation group will be performed to evaluate the contributions of different endovascular interventions. In the trial set, differences will be tested with Chi-square test. The effect of hybrid operation in the subgroup will be clarified.

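### The protocol contradicts itself on whether the trial set is randomised patients only, and neither its size of 236 nor its chi-square test is limited to randomised patients

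*Protocol article*

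**What the plan says.** On who is in the trial set, the protocol article gives two accounts.

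- **Mixed set.** Study design calls the trial set a PCT and explains: "PCT is a real-world modification of randomized clinical trial (RCT), consisting of an RCT part and a registry part". It adds: "Patients have the right to choose the part in which they want to participate".
- **Randomised set.** The abstract (Methods) states: "The assignment is based on the clinical condition in the registry set and is randomized in the trial set". Group assignment and treatment states: "In the trial set, patients who refuse the randomized group assignment will be enrolled in the registry set"; those who agree are allocated by the central randomisation system (CRS). Study design also says that the CRS produces an assignment when a participant is registered in the trial set.

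The size and the test are attached to the set without saying which account applies. Sample size, Trial set: "In total, 236 patients will be enrolled in the trial set", from a minimum of 117 per group at 38.6% versus 19%, significance level 0.05 and power 0.9. Statistical analyses: "In the trial set, differences will be tested with Chi-square test". The Discussion presents the trial set as a source of RCT-level evidence.

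Separately, Sample size, Registry set starts from the same 38.6% and says: "The aim of the hybrid operation is to reduce the rate of neural function deterioration by 10" per cent.

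**The concern.** The trial set is the only place where treatment is allocated by chance. Outside it, the choice between hybrid and traditional operation follows clinical condition and patient wishes, according to Group assignment and treatment. That is the setting for confounding by indication.

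If an analyst takes the Study design definition literally, patients with perforating feeders who chose their operation enter an unadjusted chi-square beside patients who were randomised. The result would no longer have the protection of randomisation, yet the Discussion would present it as trial evidence.

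The same ambiguity affects recruitment. Strengths and limitations says that the lower limit on the trial-set sample size must be strictly kept to maintain the level of evidence. Nobody can check that limit until it is settled who counts towards 236.

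**Working it through.** **1. The two accounts side by side.** A patient with perforating feeders declines randomisation. Under the Study design definition, this patient is in the registry part of the PCT, so in the trial set. Under Group assignment and treatment, the patient goes to the registry set. Both cannot decide whether the patient counts towards 236 and enters the chi-square. The CRS sentence in Study design fits the second account.

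**2. The plan's own sample size.** Inputs from Sample size, Trial set: p1 = 0.386, p2 = 0.19, d = 0.196, alpha 0.05, power 0.9. Two-sided testing and 1:1 allocation are assumed.

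- Variance sum V = 0.386 × 0.614 + 0.19 × 0.81 = 0.3909.
- n = (1.960 + 1.282)² × V / d² = 10.507 × 0.3909 / 0.03842 = 106.9.
- With continuity correction, n/4 × (1 + √(1 + 4/(n·d)))² = 106.9/4 × (1 + 1.0913)² = 116.9, so 117.

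The stated 117 reproduces. The pooled-variance formula gives 111, or 121 with continuity correction.

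**3. Power if all 236 are randomised (118 per arm).**

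- Pooled variance: Φ[(d√n − 1.960·√(2·p̄(1 − p̄))) / √V], with p̄ = 0.288. This is Φ[(0.196 × 10.863 − 1.960 × 0.6404) / 0.6252] = Φ(1.398) = 0.919.
- Unpooled with continuity correction: Φ[(d − 1/n) / √(V/n) − 1.960] = 0.903.

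The stated 0.9 is met either way.

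**4. Power of the randomised comparison if refusers count towards 236.** The document gives no acceptance rate, so the shares are assumptions. Both formulas use 118 × share per arm. The last column is 234 / share, rounded up.

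| Assumed share randomised | Randomised | Power, pooled | Power, continuity-corrected | Trial set needed for 234 randomised |
|---|---|---|---|---|
| 100% | 236 | 0.919 | 0.903 | 234 |
| 90% | 212 | 0.889 | 0.868 | 260 |
| 80% | 189 | 0.850 | 0.822 | 293 |
| 70% | 165 | 0.800 | 0.762 | 335 |
| 60% | 142 | 0.736 | 0.687 | 390 |
| 50% | 118 | 0.656 | 0.595 | 468 |

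Stepping down two patients at a time, power first falls below 0.9 at 220 randomised (pooled) or 232 (continuity-corrected).

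**5. The 10% reduction named for the registry, tested at 118 per arm (pooled formula).** The text does not say whether 10% is absolute or relative.

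- Absolute, 38.6% to 28.6%: power 0.37; 467 per arm would be needed for 0.9.
- Relative, 38.6% to 0.9 × 38.6% = 34.7%: power 0.09.

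**The case against.** The strongest reply is that one general sentence about what a PCT is should not outweigh the operative text. Group assignment and treatment, the abstract and the CRS sentence all point to a randomised set. Two equal groups of 117 fit chance allocation better than patient choice, and the registry part can be read as the registry set that receives refusers. This stands as the likelier intention. It does not remove the contradiction, because the size and test sentences inherit whichever definition the analyst uses.

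A reader might infer that 236 fails to deliver 0.9 power. The document does not support that. The figure reproduces, and 236 randomised patients suffice. The lower values depend on acceptance shares that appear nowhere in the text.

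A reader might also infer that confounding and lost power occur together. They belong to different analyses. Testing all 236 in a mixed set keeps roughly nominal power if the groups stay near equal, and its fault is bias. Testing only the randomised subset is unbiased but may be short of patients.

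The overlap of the registry set with the trial set is declared design, since Study design says that the registry covers the whole data pool. It is not an error in itself.

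On effect size, the 10% aim sits in the registry section and covers all enrolled lesions. The Discussion expects trial-set patients to benefit most, so a larger assumed effect there is not a contradiction. Even so, Sample size, Trial set draws its rates from bAVM studies in general and says that few exist on perforating feeders. A disclosure is therefore worth making.

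Finally, detailed analysis-set definitions may stand in an analysis plan that is not shown. Their absence here is not the fault. The fault is that this document states the membership of the set in two ways.

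**Conclusion.** The contradiction is real and bears on the study's only randomised comparison. On the mixed reading, the chi-square would include self-selected patients without adjustment and would not be the randomised evidence that the Discussion claims. The size of that bias cannot be calculated from the document.

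The 0.9 power claim is sound if 236 means randomised patients. If refusers count, it is not guaranteed: across assumed acceptance of 90% to 50%, power for the randomised comparison runs from 0.89 to 0.66 (pooled) or 0.87 to 0.59 (continuity-corrected). These figures assume two-sided 0.05, equal arms, the plan's own event rates and no losses to follow-up.

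As a secondary matter, 0.9 power holds for a 19.6-point difference. A non-significant trial-set result would not exclude a reduction of the size named for the registry.

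**What to change.** 1. Reconcile Study design with the abstract and Group assignment and treatment: define the trial set for sizing and testing as the patients randomised by the CRS.
2. State that the 236 (at least 117 per group) counts randomised patients only, and that the primary trial-set chi-square compares them in the group assigned.
3. State that patients with perforating feeders who decline randomisation are counted and analysed separately in the registry set, and that any pooled result is stratified by mode of assignment.
4. Add to the sample size section that 0.9 power applies to 38.6% versus 19%. Say whether the registry's 10% is absolute or relative, and give the corresponding trial-set power (about 0.37 or 0.09).

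The cost is wording. No new data items are needed. If refusers were being counted towards 236, the change would show how many randomised patients are still to be recruited.

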### Strengths and limitations

This study, consisting of a prospective real-world registry and a pragmatic clinical trial, will help clarify whether one-staged hybrid operation is a safe and efficient alternative to traditional surgical operation in the treatment of complex bAVMs. It evaluates the effect of one-staged perforating arterial embolization on the surgical resection of complex AVMs. It will help explore indications, key technologies, and workflows of one-staged hybrid operation, as well. However, this study has limitations. Varieties of factors are related to the outcome of complex AVMs. The sample size needs to be enlarged, if further subgroup analyses are required to clarify the effects of factors in details. And there is lower limit of sample size in the trial set. It needs to be critically obeyed to maintain the evidence level of this set.

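### The randomised comparison estimates the effect of a hybrid package, so it cannot isolate the contribution of embolization that the protocol promises

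*Protocol article*

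**What the plan says.** The Study design section gives the trial set two purposes: to validate the benefits and risks of hybrid operation "for lesions with perforating arterial feeders and the contribution of endovascular embolization". Strengths and limitations makes a similar claim for the study as a whole, and names the vessel type that defines the trial-set population: "It evaluates the effect of one-staged perforating arterial embolization on the surgical resection of complex AVMs".

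The randomised contrast has two arms: "Patients who agree to take part in the RCT part will be randomly assigned to the HO or TO group and receive the corresponding treatment". Group assignment and treatment defines them. For HO: "Patients in the HO group will receive microsurgical operation under the assistance of endovascular embolization or balloon occlusion". For TO: "Patients in the TO group will receive only traditional microsurgical operations, and a repeated DSA will be arranged 3 days after the operation". The same section adds: "The interventions of each group will be the same in the two sets". The HO definition, with its two alternatives, therefore applies to randomised patients.

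Statistical analyses plans a chi-square test for the trial set and univariate and multivariate logistic regression to explore how outcome relates to the variables listed earlier in that section. It then says: "Analyses of subgroups in the hybrid operation group will be performed to evaluate the contributions of different endovascular interventions".

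**The concern.** The stated purpose names one component, and the randomised arm contains a choice between two. A patient allocated to HO may have balloon occlusion in place of embolization, so a favourable HO versus TO result need not be due to embolization. The Discussion says the trial set could give high-level evidence as an RCT. A statement about embolization drawn from it would carry the authority of randomisation without having been randomised.

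The within-hybrid subgroup analysis does not close the gap. Patients are not randomised to technique, and no rule for the choice is given, so a difference between techniques may reflect which lesions received which technique. Strengths and limitations notes that many factors relate to outcome and that further subgroup analyses would need a larger sample. More patients improve precision but do not remove confounding.

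**Working it through.** **1. What the sample size is for.** Inputs from Sample size, Trial set: 38.6% (TO), 19% (HO), significance level 0.05, power 0.9. Taking the test as two-sided (the text does not say) with unpooled variance:

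n = [0.386 × 0.614 + 0.19 × 0.81] × (1.960 + 1.282)² / 0.196² = 106.9.

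With continuity correction: n/4 × (1 + √(1 + 4/(n × 0.196)))² = 116.9, so 117 per group. This reproduces the stated figure. Twice 117 is 234; the plan enrols 236, or 118 per arm. The calculation concerns HO versus TO as whole arms. No figure is given for embolization versus balloon occlusion.

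**2. What HO versus TO can identify.** Let s be the share of HO patients who receive embolization (not in the documents), and pE and pB the deterioration rates with embolization and with balloon occlusion. The HO rate is s × pE + (1 − s) × pB. Take s = 0.5 as an assumption:

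- pE = 19%, pB = 19%: HO rate 19%
- pE = 10%, pB = 28%: 0.5 × 10 + 0.5 × 28 = 19%
- pE = 28%, pB = 10%: 0.5 × 28 + 0.5 × 10 = 19%

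All three give the same randomised difference, 38.6 − 19 = 19.6 points. The randomised result cannot tell them apart.

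**3. What the within-hybrid comparison can show.** This example uses assumed inputs and no true difference between techniques. Let half the hybrid patients be high risk (28%) and half low risk (10%), averaging 19%. If embolization is used in 40% of high-risk and 80% of low-risk patients:

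- embolization: (0.5 × 0.4 × 28 + 0.5 × 0.8 × 10) / 0.6 = 16.0%
- balloon occlusion: (0.5 × 0.6 × 28 + 0.5 × 0.2 × 10) / 0.4 = 23.5%

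The spurious gap is 7.5 points. With use of 50% and 70% the rates are 17.5% and 21.25%, a gap of 3.75 points. With equal use in both strata it is zero, and with the pattern reversed its sign reverses. The gap does not depend on the number of patients. Within each stratum it disappears, which is the case for adjustment.

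**4. Precision in the trial set.** Two-proportion z-test, two-sided 0.05, among 118 HO patients. The embolization/balloon splits are assumed.

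| Split | Power, 19% vs 38.6% | Power, 19% vs 28.8% (half the difference) |
|---|---|---|
| 59/59 | 66% | 24% |
| 83/35 | 61% | 23% |
| 94/24 | 53% | 20% |
| 106/12 | 37% | 15% |

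Even setting confounding aside, the trial-set hybrid arm is too small to separate the techniques with confidence.

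**The case against.** The strongest reply is that HO versus TO does speak to the contribution of the endovascular step. Both arms have microsurgery, and navigation and Doppler ultrasound are used in all operations, so the stated treatment difference is the endovascular assistance. This stands. What the contrast cannot do is divide the benefit between embolization and balloon occlusion, and that matters only as far as balloon occlusion is used. The documents do not give that share.

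It can also be said that the subgroup sentence is not tied to the trial set and that the document calls the study a real-world exploration. Both are correct, and no confirmatory claim is attached to the subgroups. But then the trial set has no named analysis for its second purpose, and the subgroup sentence still sets out to evaluate contributions.

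Three stronger readings are tempting and are not supported:

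- A reader might infer that the subgroup comparison will be unadjusted. The text names no test or model for it, the sentence follows the planned regression, and such detail may sit in an analysis plan that is not shown. Only the absence of a stated link can be said.
- A reader might infer that the surgeon picks the technique according to lesion difficulty. No section says who chooses or by what rule. Only that technique is not randomised can be said.
- A reader might want to attach a false-positive rate to the subgroup comparison. Any such rate would rest on assumed risks, and would differ greatly between the 800 hybrid patients planned for the registry and the roughly 118 in the trial set.

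**Conclusion.** The concern holds as a mismatch between a stated purpose and the design. The randomised comparison estimates the effect of the hybrid package against microsurgery alone and cannot isolate embolization. The one analysis named for separating the techniques is non-randomised. This follows from the arm definitions and needs no assumed figure.

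It would lose its force if every randomised HO patient received embolization, but the arm definition does not require that. The spurious gaps of 3.75 and 7.5 points and the power of 15% to 66% are illustrations on assumed risks and splits, not predictions.

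The primary HO versus TO comparison, its chi-square test and its sample size are not affected. The point is minor and concerns what may be concluded.

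**What to change.** In Study design and in Strengths and limitations, state that the trial set estimates the effect of the hybrid package (microsurgery with embolization or balloon occlusion) against microsurgery alone, and remove the claim that it shows the effect of embolization.

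In Statistical analyses, tie the technique question to the multivariable logistic model already planned. Within the hybrid group, enter technique as a term, with a category for patients who had both if there are any. Adjust for admission mRS, Spetzler-Martin grade, feeder type and eloquence. Report estimates with confidence intervals as non-randomised association, not as proof of a technique's contribution.

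No new data are needed. Admission mRS, feeder type and eloquence are listed in that section, Spetzler-Martin grade is known from eligibility, and endovascular materials are recorded for each operation. The shared pool supports the model better than the trial set alone: at the planned 19%, 118 hybrid patients give about 22 events (0.19 × 118), and 800 would give 152 (0.19 × 800).

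The cost is a few sentences and a weaker claim about embolization. Treatment, randomisation and sample size do not change.
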